#### Education

*The Back Pain Helpbook* [68] is given to individuals randomized to the education group. This book has been used successfully in previous cLBP studies for educational purposes [32, 80]. The book includes information on how back pain is influenced by posture, emotions, fear avoidance behaviors, and social support. It also encourages pain self-management strategies such as mind-body relaxation techniques, exercise programs, and medications. In addition, Veterans receive a handout after randomization suggesting specific chapters to read throughout the intervention period and brief mailed newsletters every three weeks that highlight main points from the recommended chapters (see Additional file 7). Check-in calls, which are proceeded by a newsletter mailing, are conducted by research staff every three weeks to assess progress and reinforce study retention efforts.

### Data collection

Outcome data are collected at baseline, 6 weeks, 12 weeks, and 24 weeks. Participants in both treatment arms complete paper surveys in person and receive cash honoraria after the completion of each survey. We give $25 at baseline, 6 weeks, and 12 weeks. At the final follow-up at 24 weeks, participants receive $50 after completion of their survey. Paper surveys are double-entered into StudyTRAX™ by research staff who have no knowledge of or access to identifiable participant information or treatment assignment. The two data entries are compared and reconciled.

#### Outcome measures

Table 3 shows the data collection schedule. Our measures include core patient-oriented outcomes for the cLBP trials, including those recommended by the Report of the NIH Task Force on Research Standards for Chronic Low Back Pain [73]. Change in pain intensity and back-related function are the two co-primary outcomes at 12 weeks [63, 71]. Secondary back pain outcomes include pain medicine use in the previous week, including medication class and dosage [81]; health-related quality of life (SF-12) [82]; pain interference [83]; overall improvement (7-point Likert scale, 0 = extremely worsened to 6 = extremely improved); and patient satisfaction with cLBP treatment (5-point Likert scale, 1 = very satisfied to 5 = very dissatisfied) [84]. Psychological secondary outcomes include post-traumatic stress symptoms (PCL-C) [85] and depression symptoms measured using the 9-item Patient Health Questionnaire (PHQ-9) [86]. The Pittsburgh Sleep Quality Index (PSQI) is also administered [87]. Exploratory neuropsychological outcomes include post-concussive symptoms measured using the Neurobehavioral Symptom Inventory (NSI) [88], 7-item Generalized Anxiety Disorder questionnaire (GAD-7) [89], Coping Strategies Questionnaire (CSQ) [90], and Pain Self-Efficacy Questionnaire (PSEQ) [91]. Exploratory social outcomes include marital/family functioning measured using the Dyadic Adjustment Scale (DAS) [92], employment status (Work Productivity and Activity Impairment questionnaire) [93], and housing status. NIH PROMIS® (Patient Reported Outcomes Measurement Information System) tools [94] for outcomes of interest, such as pain, function, depression, anxiety, and sleep, are used to assess how well they correlate with the DVPRS, RMDQ, PHQ-9, GAD-7, and PSQI. At baseline, we also gather standard sociodemographic information and possible covariates, including race, ethnicity, income, education, military service history, medical comorbidities, back pain history, expectation of helpfulness for the different interventions [95], and preference of treatment assignment.

**Table 3 Tab3:** Schedule of assessments

Measures	Enrollment	Baseline	6 weeks	12 weeks	24 weeks
Screening and enrollment					
Eligibility screening	✓				
Informed consent	✓				
Baseline information					
Sociodemographics*		✓			
Expectations and preference		✓			
Back pain history and comorbidities		✓			
Primary outcomes					
Low back pain intensity (DVPRS)		✓	✓	✓	✓
Back-related function (RMDQ)		✓	✓	✓	✓
Secondary outcomes					
Pain medication use		✓	✓	✓	✓
PTSD CheckList—Civilian version (PCL-C)		✓	✓	✓	✓
Health-related quality of life (SF-12)		✓	✓	✓	✓
Satisfaction with treatment		✓	✓	✓	✓
Global improvement			✓	✓	✓
Cost-effectiveness outcomes					
Work productivity		✓	✓	✓	✓
Medical utilization and cost		✓	✓	✓	✓
Exploratory outcomes					
PROMIS-29 and pain interference		✓	✓	✓	✓
Depression (PHQ-9) and anxiety (GAD-7)		✓	✓	✓	✓
Relationship satisfaction (DAS)		✓		✓	✓
Pain self-efficacy (PSEQ)		✓		✓	✓
Sleep quality (PSQI)		✓		✓	✓
Coping strategies (CSQ)		✓		✓	✓
Post-concussive symptoms (NSI)		✓		✓	✓
Possible covariates and confounders					
Exercise history		✓	✓	✓	✓
Low back pain treatments		✓	✓	✓	✓
Alcohol, drugs, and smoking		✓		✓	✓

*Sociodemographic information includes gender, age, relationship status, ethnicity, race, income, housing, education level, and military service history

DVPRS = Defense and Veterans Pain Rating Scale; RMDQ = Roland Morris Disability Questionnaire; PROMIS = Patient Reported Outcome Measurement Information System; SF-12 = Short Form 12-item Health Survey; PHQ-9 = 9-item Patient Health Questionnaire; GAD-7 = 7-item General Anxiety Disorder survey; DAS = Dyadic Adjustment Scale; PSQI = Pittsburgh Sleep Quality Index; NSI = Neurobehavioral Symptom Inventory

#### Cost-effectiveness

We use a multi-method approach to collect cost data at baseline, 6 weeks, 12 weeks, and 24 weeks. Since our interventions may influence other common comorbidities of cLBP (e.g., depression [52]), we measure both back-related utilization and total medical utilization. Direct medical costs are measured and consist of the cost of (1) implementing the interventions themselves and (2) ongoing medical utilization before, during, and after the intervention. Intervention implementation costs (e.g., non-study-specific staff hours, materials, facility use) are captured from study records and valued at their actual costs. Ongoing total VA medical utilization including visits, hospitalizations, tests, radiology, and medications are taken directly from the electronic medical record system. Direct medical costs are valued at their actual costs to the VA. Any non-VA medical utilization (e.g., chiropractors, out-of-pocket back-related expenses) is obtained from a cost questionnaire completed by the Veteran with the primary initial recall period being the past 6 weeks and is valued at the reported actual price paid by Veterans. Indirect costs (i.e., lost productivity) for employed Veterans will be calculated as the number of lost productive hours (as reported in the Work Productivity and Activity Impairment questionnaire) multiplied by a national average cost of employment for each Veteran’s general job category. Lost productivity costs for those not in the work force are assumed to be captured by their report of overall quality of life [96]. Lost productivity costs for those looking for work will be considered in the sensitivity analyses.

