### Specific aims

This study will determine if yoga can become a safe, clinically effective, cost-effective, and scalable nonpharmacologic approach to address the physical and psychosocial dimensions of cLBP in Veterans [67]. This study is a 24-week two-arm randomized controlled trial for 120 Veterans with cLBP with four specific aims:Primary aim – to determine the effectiveness of a structured, reproducible 12-week series of hatha yoga classes, supplemented with home practice, compared to an education control group, for decreasing pain intensity and improving back-related functionSecondary aim – to evaluate the effectiveness of yoga compared to education for improving PTSS and other psychosocial outcomes, including depression, anxiety, self-efficacy, and copingSecondary aim – to evaluate the cost-effectiveness of yoga for cLBP at 12 weeks and 24 weeks from three perspectives: the Veteran, the Veterans Health Administration, and societyExploratory aim – to explore the effect of cLBP on family relationships, as well as yoga’s impact on the Veteran, family, and family functioning

The results of this study have the potential to impact the approach and management of cLBP according to the Army Surgeon General Pain Management Task Force vision, i.e., having a more integrative and interdisciplinary focus on active self-care approaches that empower Veterans to have greater control of their condition [63].

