#### Cost-effectiveness analyses

All cost-effectiveness analyses will use the intention-to-treat principle. Quality-adjusted life-years (QALYs) will be calculated from the results of the SF-12 based on an algorithm developed by Brazier et al. [99] For the Veteran perspective, we will compare Veterans' incremental out-of-pocket costs (e.g., transportation, over-the-counter medications, and co-payments) to their incremental QALY impacts. For the VHA perspective, incremental direct intervention costs will be compared to ongoing direct medical utilization costs. This cost-benefit analysis will address whether, economically, yoga should be a treatment option for the VA population. For the society perspective, we will conduct a cost-utility analysis by comparing the incremental societal costs for each treatment arm (i.e., direct medical, nonmedical, and productivity costs) to the incremental change in QALYs [100]. We will use bootstrap methods to calculate confidence intervals [101] and perform one-way sensitivity analyses to determine the robustness of our estimates with different assumptions used to value productivity [102]. Combined non-back pain and back pain-related utilization will be used for all of these analyses. We will also perform sensitivity analyses using only back pain-related utilization.

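### Direct medical cost is defined to include utilization before the intervention, and the cost-effectiveness analyses neither exclude that part nor name baseline cost as a covariate

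*Protocol article*

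**What the plan says.** In the protocol article, the Cost-effectiveness section under Data collection makes direct medical cost the total of two parts. One is the cost of delivering the study treatments; the other is "ongoing medical utilization before, during, and after the intervention". The trial will "collect cost data at baseline, 6 weeks, 12 weeks, and 24 weeks". VA utilization comes from the electronic record, with no look-back length given. Non-VA utilization comes from a questionnaire, "with the primary initial recall period being the past 6 weeks".

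Cost-effectiveness analyses then uses these quantities. For the VHA, "incremental direct intervention costs will be compared to ongoing direct medical utilization costs". For society, the analysis is a cost-utility comparison, "comparing the incremental societal costs for each treatment arm (i.e., direct medical, nonmedical, and productivity costs) to the incremental change in QALYs". On scope it says: "Combined non-back pain and back pain-related utilization will be used for all of these analyses". Intervals are to come from the bootstrap. No accumulation window and no baseline-cost term is given.

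Three other places bear on the point:

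- Specific aims states the aim as "to evaluate the cost-effectiveness of yoga for cLBP at 12 weeks and 24 weeks from three perspectives".
- Table 3 lists medical utilization and cost, including the baseline collection, among the cost-effectiveness outcomes. Its separate block of possible covariates and confounders does not include it.
- The opening of Data analysis has a general rule: baseline characteristics are compared between arms at α = 0.1, and later analyses adjust for those that differ.

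**The concern.** Treatment cannot change cost incurred before randomization. If that cost is part of the outcome, it brings no treatment signal, only whatever difference chance has put between the arms. In one trial that difference would be reported as a saving or a cost of yoga. The VHA analysis is meant to inform whether yoga is offered in the VA, and its main version uses all utilization, including hospitalizations and care unrelated to the back. A few high-cost Veterans could therefore move an arm mean when there are 60 per arm.

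The same pre-intervention cost is a natural predictor of later cost. As a covariate it would narrow the interval; inside the total it widens it.

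**Working it through.** **Plan's own figure.** The protocol states no SD, precision or sample size for cost, so there is nothing to reproduce. The check is therefore relative.

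**Inputs from the protocol.** 120 Veterans randomized 1:1, so 60 per arm; with the 20 % dropout assumed under Sample size, 60 × 0.8 = 48 per arm.

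**Assumptions, not in the documents.** k = SD of pre-intervention cost ÷ SD of post-randomization cost, 0.25 to 1. ρ = correlation between the two, 0 to 0.7. A value of k below 1 is plausible because the one stated recall period is 6 weeks, against horizons of 12 and 24 weeks.

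**Formulas.** In units of 2σ²/n, with σ the SD of post-randomization cost, the variance of the arm difference is:

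- post-randomization cost only: 1
- pre-intervention cost summed in: 1 + k² + 2ρk
- pre-intervention cost as covariate: 1 − ρ²
- change from baseline: 1 + k² − 2ρk

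The summed variance equals (1 − ρ²) + (k + ρ)² and the change-score variance equals (1 − ρ²) + (k − ρ)². So, apart from a small degrees-of-freedom cost, covariate adjustment is never less precise than either.

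**Standard-error ratios.**

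| k | ρ | summed ÷ post-only | summed ÷ covariate |
|---|---|---|---|
| 0.25 | 0 | 1.03 | 1.03 |
| 0.25 | 0.5 | 1.15 | 1.32 |
| 0.25 | 0.7 | 1.19 | 1.66 |
| 0.5 | 0 | 1.12 | 1.12 |
| 0.5 | 0.5 | 1.32 | 1.53 |
| 0.5 | 0.7 | 1.40 | 1.96 |
| 1 | 0 | 1.41 | 1.41 |
| 1 | 0.5 | 1.73 | 2.00 |
| 1 | 0.7 | 1.84 | 2.58 |

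Worked example for the last row: √(1 + 1 + 1.4) = √3.4 = 1.84; √(1 − 0.49) = 0.714; 1.84 ÷ 0.714 = 2.58.

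**Skewed costs.** A simulation used lognormal cost with a coefficient of variation of 1.5, 48 per arm, ρ = 0.5 and percentile-bootstrap intervals (150 trials, 200 resamples each). For k = 0.25, 0.5 and 1, the summed interval was 1.15, 1.32 and 1.81 times as wide as post-only, and 1.42, 1.70 and 2.29 times as wide as covariate-adjusted.

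**Chance imbalance.** The arm difference in pre-intervention cost has standard error √(2/60) = 0.18 pre-cost SDs (95 % range about ±0.36), or √(2/48) = 0.20 (±0.40) at 48 per arm.

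**If nothing is summed.** Against covariate adjustment, an unadjusted post-randomization comparison has a standard error 1/√(1 − ρ²) times as large: 1.00 at ρ = 0 and 1.40 at ρ = 0.7. A change-from-baseline analysis has 0.74 to 1.41 times the post-only standard error over the grid k = 0.25, 0.5, 1 and ρ = 0, 0.3, 0.5, 0.7.

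**The case against.** The strongest reply is that the sentence describes what is collected. It sits under Data collection and goes on to name sources. The analysis section never says that pre-intervention cost is added to the arm totals, and the aim is set at 12 and 24 weeks. Collecting utilization before, during and after is also what one would do in order to use baseline cost properly. This stands. A reader might infer that the plan has committed itself to summing pre-intervention cost into the result; the documents do not support that, because they leave the accumulation window open.

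A reader might also infer that, if before is only a collection window, the comparison is a raw arm difference. That is not stated either. Incremental cost, set beside incremental change in QALYs, can be read as change from baseline. The α = 0.1 rule could also bring baseline cost into the model if cost is among the variables tested and differs.

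Finally, a journal article may leave covariates to a fuller document. The absence of a named covariate would not be a finding on its own. What remains is that the published definition, taken at its word, includes cost outside the stated horizon, and no section reconciles the two. The α = 0.1 rule does not take that cost out of the total. It also makes adjustment depend on a chance imbalance, whereas the gain from a prognostic covariate does not.

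**Conclusion.** The point holds as a defect in the wording of a secondary-aim analysis. The definition of direct medical cost includes pre-intervention utilization, the VHA and societal analyses use that cost without exclusion, and the horizon in Specific aims does not cover it. Followed literally, this multiplies the standard error by 1.03 to 1.84 against post-randomization cost only and by 1.03 to 2.58 against covariate adjustment. Both ranges rest wholly on the assumed SD ratio (0.25 to 1) and correlation (0 to 0.7).

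The direction is firm under the literal reading for any non-negative correlation; the size is not. A doubling of the standard error is tempting to report, but it is the covariate comparison at k = 1 and ρ = 0.5, and equal pre and post SDs have no support in the documents. Nor should a reader infer systematic bias: randomization balances pre-intervention cost in expectation, so what is added is noise. The co-primary outcomes and the sample size are unaffected.

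**What to change.** In Cost-effectiveness, keep pre-intervention utilization as collected data but take it out of the definition of the cost outcome. In Cost-effectiveness analyses, state that:

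1. incremental direct medical cost, for the VHA and societal perspectives, counts only cost from randomization to 12 weeks and to 24 weeks;
2. each Veteran's pre-intervention utilization cost, over a look-back of fixed, stated length ending at randomization, is always a covariate in the incremental-cost regression, together with the three stratification factors (age, PCL-C and partnered status), whatever a baseline test shows;
3. the bootstrap is applied to that adjusted difference, with the regression refitted in each resample;
4. raw arm means are tabulated alongside.

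The cost is a few sentences and a few model terms. The protocol already provides for the VA record and the baseline cost questionnaire. The one drawback is that an adjusted cost difference is a little harder to present than raw means, which the added table answers.

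### The societal cost-utility analysis values non-VA care only at the price the Veteran paid, so the part of that care paid by third parties is left out

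*Protocol article*

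**What the plan says.** The Cost-effectiveness section under Data collection sets the valuation rules.

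- **VA care.** Utilization comes from the electronic medical record, and "Direct medical costs are valued at their actual costs to the VA".
- **Non-VA care.** "Any non-VA medical utilization (e.g., chiropractors, out-of-pocket back-related expenses) is obtained from a cost questionnaire completed by the Veteran", and this care "is valued at the reported actual price paid by Veterans".

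The Cost-effectiveness analyses section under Data analysis then says how the costs are used.

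- **Veteran perspective.** It compares the Veteran's "incremental out-of-pocket costs (e.g., transportation, over-the-counter medications, and co-payments) to their incremental QALY impacts".
- **Societal perspective.** It is a cost-utility analysis "comparing the incremental societal costs for each treatment arm (i.e., direct medical, nonmedical, and productivity costs) to the incremental change in QALYs".
- **Scope of care.** "Combined non-back pain and back pain-related utilization will be used for all of these analyses".
- **Sensitivity.** The authors will "perform one-way sensitivity analyses to determine the robustness of our estimates with different assumptions used to value productivity". A further analysis restricts utilization to back-related care. The Cost-effectiveness section adds a sensitivity analysis on lost productivity of Veterans looking for work.

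Cost-effectiveness from the Veteran, VHA and societal perspectives is a secondary aim under Specific aims.

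**The concern.** Price paid by the Veteran is the right measure when the question is what the Veteran spends. A societal analysis asks what resources were used, whoever paid for them. Applied to the societal total, the rule adds VA care at full cost to non-VA care at the patient's share only. A non-VA visit covered in part by an insurer enters at the co-payment, and one covered in full enters at nothing.

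At stake is how the societal result is read. If one arm used less third-party-paid non-VA care, that saving to society would be missed; if it used more, the extra cost would be missed. If use shifted from the VA to insured outside care in one arm, the VA cost would drop out and little would replace it. These are possibilities that the rule leaves open. The article does not predict any of them.

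**Working it through.** The article reports no cost figure, so there is nothing to reproduce. The check is a comparison of the stated rules followed by simple algebra.

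**Step 1: does the rule fit each perspective?**

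| Perspective | Costs to be counted | Value given to non-VA care | Fit |
|---|---|---|---|
| Veteran | Out-of-pocket costs, including co-payments | Price paid by the Veteran | Yes |
| Society | Direct medical, nonmedical and productivity costs | Price paid by the Veteran (no other rule given) | Only for care that the Veteran pays for in full |

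**Step 2: is the mismatch picked up elsewhere?** The sensitivity analyses vary how productivity is valued, how job-seekers are treated, and whether all or only back-related utilization counts. None changes the price attached to a non-VA service.

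**Step 3: effect on the level in one arm.** Let C be the full non-VA cost per participant and s the share paid by the Veteran. The article gives neither.

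- Counted cost = s × C
- Omitted cost = (1 − s) × C

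The omitted fraction of non-VA cost is 100 % at s = 0, 75 % at s = 0.25, 50 % at s = 0.5 and 0 % at s = 1. These are fractions of this one component. Total societal cost also includes intervention, VA, nonmedical and productivity costs.

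**Step 4: effect on the increment.** Write Y for yoga and E for education. With the same s in both arms:

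- True increment = C_Y − C_E
- Counted increment = s × (C_Y − C_E)
- Error (counted − true) = −(1 − s) × (C_Y − C_E)

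As an illustration with assumed values, take C_Y = $400 and C_E = $600. The true increment from this component is 400 − 600 = −$200.

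| s (assumed) | Counted, yoga | Counted, education | Counted increment | Error |
|---|---|---|---|---|
| 0 | $0 | $0 | $0 | +$200 |
| 0.25 | $100 | $150 | −$50 | +$150 |
| 0.5 | $200 | $300 | −$100 | +$100 |
| 1 | $400 | $600 | −$200 | $0 |

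If the two costs are exchanged, so that yoga has the higher non-VA cost, every sign reverses. If C and s are equal in both arms, the error in the increment is zero. If s differs between arms, the error is −[(1 − s_Y) × C_Y − (1 − s_E) × C_E]. In every case it depends on the between-arm difference in third-party-paid cost.

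**The case against.** The best case for the plan has five parts.

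1. **The category may be small or mostly self-paid.** The article's examples of non-VA use are chiropractors and out-of-pocket back-related expenses. Where the Veteran pays the whole price, price paid is the full price. Visits, hospital stays, tests, radiology and medications are listed under VA utilization and valued at VA cost. This stands as a limit on size. It does not remove the mismatch: the rule covers all non-VA medical use, and back-related and other care are combined in every analysis, so insured outside care is in scope.

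2. **Randomization may balance the omission.** A reader might infer that the societal result itself is understated, or that it is tilted for or against yoga. The documents do not support either reading. The planned result is an increment, and an omission that is equal in both arms cancels. This stands. Balance is not guaranteed, however, because the article measures total utilization on the ground that the interventions may affect comorbidities as well as back pain.

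3. **Insured care is not all counted as zero.** Only the third-party-paid portion is lost; partly covered care enters at the co-payment. Outside care that the VA itself pays for may be captured under VA cost, though the text does not say so. This stands.

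4. **The percentages rest on assumption.** The share s is a chosen range, and no effect on cost per QALY can be estimated. This stands.

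5. **Unit-cost detail usually sits in a fuller economic plan.** That would answer a complaint about missing detail. Here the article states a rule, and the rule does not suit one of the perspectives that it names.

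**Conclusion.** The point holds in a conditional form. The article fixes a valuation of non-VA care that suits the Veteran perspective and does not suit the societal one, and no planned sensitivity analysis addresses it. The level of societal cost is understated in each arm to the extent that third-party-paid non-VA care is used. The incremental societal cost and the cost per QALY are biased if that care differs in cost between arms.

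Neither direction nor size can be determined, because the article gives no volume of insured non-VA care, no Veteran share and no expected difference between arms. The dollar figures in the working show the mechanism and are not estimates for this trial.

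The matter is confined to one component of one of three perspectives within a secondary aim. It should be corrected, but it does not touch the co-primary outcomes, the sample size or the Veteran-perspective analysis.

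**What to change.** - Restrict price paid by the Veteran to the Veteran perspective.
- For the societal perspective, value each reported non-VA service at a full unit cost covering all payers, for example the VA cost of the same service or a published fee schedule. Use price paid only for items bought wholly out of pocket.
- Add a sensitivity analysis over a range of these unit costs.
- Confirm that the cost questionnaire records quantities by service. The article says that it collects non-VA utilization but does not show at what level of detail. According to Trial status, recruitment is still under way, so a gap could be closed for surveys yet to be completed.

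The cost is a change of wording in the economic analysis plan and a unit-cost table, plus a questionnaire change if quantities are not recorded. The downside is that unit costs are approximations that replace reported prices, which is why the sensitivity range is needed.
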